### Treatments administered

Patients are randomly assigned to groups to either receive a high-dose JWYH by oral administration, a low-dose JWYH by oral administration, or a placebo twice daily for 4 weeks (28 days). After baseline assessment, all participants will maintain or receive background therapy with ICS or a β_2_-adrenoceptor agonist as usual care.

Participants in the high-JWYH-formula group receive 18.5 g JWYH granules twice daily for 4 weeks, whereas participants in the low-JWYH-formula group receive 9.25 g of JWYH granules twice daily for 4 weeks. Patients in the placebo group are given placebo granules (9.25 g twice daily for 4 weeks). Drugs are identical in appearance, shape, size, and packaging.

Whole ingredients of the intervention formula include *Rehmanniae Radix Praeparata* (*Shu Di Huang*) 15 g, *Cinnamomi Cortex* (*Rou Gui*) 3 g, *Ephedrae Herba* (*Ma Huang*) 4.5 g, *Cervi Cornus Colla* (*Lu Jiao Jiao*) 3 g, *Sinapis Semen* (*Bai Jie Zi*) 6 g, *Zingiberis Rhizoma Preparatum* (*Pao Jiang*) 6 g, *Clycyrrhizae Radix Et Rhizoma* (*Gan Cao*) 6 g, *Asari Radix Rhizoma* (*Xi Xin*) 3 g, and *Codonopsis Radix* (*Dang Shen*) 9 g. All herbal granules are produced by the Sichuan Green Pharmaceutical Technology Development Limited by Share Ltd. in Sichuan, China. The dosage for all three groups includes one pack of granules that needs to be soaked in 100 mL of boiling water, taken orally twice daily, after breakfast and supper.

At each study visit, adherence to intervention is monitored and participants are asked to return all study containers with any unused packs of granules, including all empty containers. Once the patient is randomized, study sites will take every reasonable effort to follow the patient for the entire course of the study. All examination and transportation costs are covered and the results of symptoms and physical examinations will be explained at every visit. Prior to every visit, messages will be sent through WeChat or by phone to remind patients of the upcoming data collection.

Patients who discontinue the assigned treatment based on serious adverse events (SAEs), or poor compliance (more than 14 days without taking medicine), or in cases when the attending physician requests that the patient should undergo orally or intravenously administered corticosteroid therapy because symptoms worsen after screening.

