### Data collection and management

After screening and completing a set of questionnaires and evaluations, participants will attend two assessment visits and three follow-up visits (Fig. 2). Demographic information (date of birth, gender, etc.) and medical condition (medical history, concomitant medication, etc.) are recorded.

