### Statistical methods

The modified intent-to-treat (mITT) population is defined as randomized patients who receive at least one dose of randomized treatment with at least one post-randomization ACT value, classified according to their assigned treatment. The mITT analysis set is used for efficacy and exploratory analyses. Last observation carried forward (LOCF) imputation is used for missing data in the mITT population. A per-protocol (PP) population is defined as randomized patients without major protocol violations. The PP analysis set is used to repeat the efficacy analysis and to assess the robustness of the results. The safety population is defined as all patients who receive at least one dose of randomized treatment and for whom any post-dose data are available, classified according to the treatment received. The safety population will be used for the analyses of all safety measures.

For the primary outcome, changes in ACT scores from baseline to week 4 will be analyzed by means of analysis of covariance (ANCOVA). Treatment and center interactions will be examined, and, when an interaction does not exist, the ANCOVA model includes treatment and baseline ACT total score as explanatory variables. Otherwise, ANCOVA analysis will include the baseline ACT total score as covariate, treatment as a fixed effect, and the center as a random effect. Secondary outcomes (ACT at 8 weeks, FEV_1_, and FVC) are assessed in a similar fashion. AER will be analyzed using a *t* test or Wilcoxon rank-sum test as appropriate, and the Holm-Bonferroni method is used to control type I errors if necessary.

A mixed-model repeated measures (MMRM) analysis will be used to assess PEF changes. Comparisons will be based upon the contrast between treatments at week 4 (day 28) and week 8 (day 56). Model-based point estimates, 95% confidence intervals, and *p* values will be calculated. A *p* value < 0.05 is considered statistically significant.

For exploratory analysis, MMRM analysis uses all available ACT total score through the week 16 (day 112) visit, and comparisons will be based upon the contrast between treatments at week 16 (day 112). Model-based point estimates, 95% CIs, and *p* values are calculated.

Any adverse event will be recorded in the CRF regardless of relationship to the study intervention. Safety endpoints will be analyzed using summary statistics (frequency, count, percentage).

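### The planned tests of the week-8 asthma exacerbation rate make no stated use of follow-up time, give no rate ratio, and run on a set whose entry depends on an ACT value, so they can mislead if follow-up differs between arms

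*Protocol article*

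**What the plan says.** Under Secondary outcomes, the protocol article lists AER at week 8. It does not say whether this is a count, a proportion or events per unit of time.

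Under Statistical methods, AER is to be compared by a t "test or Wilcoxon rank-sum test as appropriate, and the Holm-Bonferroni method is used to control type I errors if necessary". In the same section, ACT at 8 weeks, FEV1 and FVC are analysed by covariance analysis with a baseline term, and PEF by a repeated-measures model. AER alone gets an unadjusted two-sample test.

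Three general rules in that section also reach AER:

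- "The mITT analysis set is used for efficacy and exploratory analyses".
- Entry to that set requires a dose of study treatment, and patients "with at least one post-randomization ACT value, classified according to their assigned treatment".
- "Last observation carried forward (LOCF) imputation is used for missing data in the mITT population".

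Under Treatments administered, one ground for stopping assigned treatment is that the physician "requests that the patient should undergo orally or intravenously administered corticosteroid therapy because symptoms worsen after screening". The same section adds: "Once the patient is randomized, study sites will take every reasonable effort to follow the patient for the entire course of the study".

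**The concern.** Exacerbations over 8 weeks are likely to be a sparse count, and some patients will be observed for less than 8 weeks, since the plan itself allows for 20% dropout. A test on raw counts treats a patient seen for one week without an event like a patient seen for eight. If one arm loses more patients or loses them earlier, it shows fewer events for that reason alone. The direction of the error then depends on which arm loses more.

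A t test gives a difference in means and a Wilcoxon test a comparison of ranks. Neither gives the rate ratio that an outcome called a rate invites.

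The analysis set adds a second problem. Whether an exacerbation counts depends on whether a questionnaire was completed after randomization, and that has nothing to do with whether the event occurred.

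**Working it through.** **1. The plan's own figure.** The article gives no assumption for AER. Its sample size (ACT difference 2, SD 4, two-sided 5%, 80% power) reproduces: 2 × (1.96 + 0.842)² × 4² / 2² = 62.8, so 63 by the normal approximation; the t-based value is 63.8, so 64. Then 64 / 0.80 = 80 per arm, and 3 × 80 = 240. This has no bearing on AER, but it supplies the 80 per arm and the 20% dropout used below.

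**2. Exposure arithmetic.** Assume equal true event rates and dropout spread evenly over the 8 weeks. Mean exposure is then 1 − d/2 of the window for dropout share d.

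- 10% versus 30%: 0.95 versus 0.85. The ratio of mean counts is 0.85 / 0.95 = 0.895, or 0.95 / 0.85 = 1.118 the other way: about 11% apart with no effect.
- 0% versus 40%: 1.00 / 0.80 = 1.25.

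**3. Type I error by simulation.** Two arms of 80; gamma-Poisson counts with dispersion 0.5; 0.15, 0.3 or 0.6 events per patient over 8 weeks; 1,500 runs per setting. Rates, dispersion and dropout patterns are assumptions. The Monte Carlo standard error at 5% is √(0.05 × 0.95 / 1500) = 0.56 percentage points. Ranges are over the three rates, in percent:

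| Dropout by arm | t test, counts | Wilcoxon, counts | t test, per-patient rates | Poisson with offset |
|---|---|---|---|---|
| 20% / 20% | 4.0–5.2 | 4.2–5.5 | 3.3–5.1 | 4.4–5.3 |
| 10% / 30% | 6.0–7.4 | 5.7–7.5 | 4.7–5.5 | 4.3–5.5 |
| 0% / 40% | 7.7–16.6 | 8.2–17.7 | 5.1–6.4 | 4.5–5.7 |

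Under no effect the simulated mean-count ratio was 1.11–1.13 at 10%/30% and 1.25–1.27 at 0%/40%. The person-time ratio stayed near 1.00.

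**4. Power with equal 20% dropout, true ratio 0.5.** At placebo rates 0.15 / 0.3 / 0.6, the t test on counts had 25 / 43 / 64% and the offset model 22 / 44 / 67%. The mean-count ratio was 0.50–0.51. In this setting little is lost.

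**5. Wilcoxon on per-patient rates.** Dividing by follow-up does not help event-free patients: zero over one week still ties with zero over eight. With Poisson counts, the share at zero is exp(−0.1) = 0.90 at 0.1 events per patient and exp(−0.3) = 0.74 at 0.3. In a separate simulation (4,000 runs, same assumptions), type I error was 5.5–5.8% at 10%/30% dropout and 7.8–9.4% at 0%/40%. The excess at 10%/30% is small.

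**6. The entry condition.** The article describes visits only as "participants will attend two assessment visits and three follow-up visits"; the detailed schedule is in a figure not shown, so the first post-randomization ACT was assumed at week 2 or week 4. True ratio 0.5, 20% dropout in both arms:

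- If exacerbators stay in follow-up, dropping other early leavers makes no material difference (mean-count ratio 0.49–0.52).
- If every patient left at the first exacerbation, and was excluded when that came before the first ACT, the mean-count ratio was 0.51–0.59. T-test power fell from 25 / 43 / 64% to 20 / 28 / 38% (week 2) or 11 / 20 / 23% (week 4). This combines exclusion with truncated follow-up. The offset model on the same reduced set did no better overall (14 / 25 / 37% and 13 / 16 / 21%), so changing the test alone does not recover lost events.

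**The case against.** The strongest reply is that the planned tests are adequate. The only dropout figure in the article is a single 20%. With that in both arms, the tests keep their level and a halved rate is recovered with power close to the offset model. At about 80 per arm, non-normal counts do not invalidate a t test. A 10% versus 30% imbalance is an assumption, and a double-blind trial need not show one. All of this stands, so a reader who infers that the planned comparison is invalid goes too far.

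Three other stronger readings are tempting and not supported.

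- **That follow-up time is certainly ignored.** AER is called a rate, and its definition may be in the full protocol or analysis plan. A t test on events divided by observed time fits the text and largely holds its level. A Wilcoxon test on the same quantity corrects only in part, and the text leaves the choice between them open.
- **That early exacerbators are dropped.** The corticosteroid criterion concerns stopping assigned treatment, and sites are asked to keep following every randomized patient. Only patients with no post-randomization ACT are lost; an exacerbator is among them only if that patient also leaves before the first one.
- **That LOCF sets later events to zero.** The rule is stated for missing data in general, and how it would act on AER is not stated. What can be said is that no exception is made for event data, where carrying a value forward has no clear meaning.

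The remedy has limits too. A model with eight centers would have 11 coefficients (intercept, two treatment terms, baseline ACT, seven center terms). At 0.1 events per patient there are about 240 × 0.1 = 24 events, or 24 × 0.9 / 8 = 2.7 per center after 20% dropout. The chance that some center has none is about 1 − (1 − exp(−2.7))⁸ = 43%, so center terms would often not be estimable. An offset also does not fully remove bias when follow-up ends because of the event: with 70% of exacerbations ending follow-up (assumed) and a true ratio of 0.5, person-time ratios were 0.55–0.56 against 0.57–0.60 for raw counts.

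**Conclusion.** The point holds as a conditional weakness in a secondary analysis. For an outcome named a rate, the article fixes tests with no stated use of observed time and no rate ratio, on a set whose entry depends on an ACT value, with LOCF applied without exception.

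With similar follow-up in the arms the harm is small. With follow-up that differs by arm, raw counts are biased by about 11% at 10% versus 30% dropout, with type I error of about 6 to 7.5%; at the extreme of 0% versus 40% it is about 8 to 18%. An offset model stays near 5% throughout. The article gives no exacerbation rate, dispersion or dropout by arm, so these sizes rest on assumptions. The effect of the entry condition runs from negligible to a marked loss of power, depending on whether exacerbators remain in follow-up.

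The change is worth making because it is cheap and must be settled before unblinding. The primary ACT conclusion is unaffected.

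**What to change.** Replace the AER sentence in Statistical methods with a definition and one model.

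- **Outcome:** number of exacerbations from randomization to week 8 over days observed in that window. Count events to the end of follow-up, including any event that led to stopping assigned treatment.
- **Set:** all randomized patients who took at least one dose, by assigned arm, whether or not an ACT value exists. State that LOCF does not apply to this outcome.
- **Model:** Poisson regression with robust standard errors (negative binomial if it converges), with treatment and baseline ACT as terms and log days followed as offset. Omit center terms if events are sparse.
- **Report:** rate ratios for each dose against placebo with 95% confidence intervals, and days observed by arm so that any imbalance is visible.
- **Fallback:** fix before unblinding what is done if events are too few for the model, for example if an arm has none.

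The cost is a few lines of text, a standard SAS procedure and slightly more analysis work, including the fallback rule. Exacerbations and dates of last contact are needed for every treated patient, which the existing follow-up commitment should already provide.

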In recent years, many studies that focus on TCM suggest that recurrent asthma has important links with wind (*Feng*), phlegm (*Tan*), blood stasis (*Yu*), and deficiency (*Xu*) [18]. In the Qing dynasty in China, a prescription of the *Yang He* (YH) formula was developed, and was commonly used for the treatment of the *Yin* and *Han* syndromes [19]. It functions in reinforcing deficiency (*Fu Zheng*), as well as dispelling wind (*Qu Feng*), removing blood stasis (*Hua Yu*), and eliminating phlegm (*Qu Tan*). Based on the empirical prescription, ingredients such as *Asari Radix Rhizoma* (*Xi Xin*) and *Codonopsis Radix* (*Dang Shen*) were added to improve the YH formula, thereby generating the *Jia Wei Yang He* (JWYH) formula [20, 21]. JWYH strengthens the function of reinforcing deficiency and resolving phlegm, and has been widely used for the treatment of chronic asthma. Our preliminary data show that the JWYH formula significantly improves cough and sputum symptoms, reduces the number of asthma episodes, and improves serum interferon (IFN)-γ levels (data not shown).

In several epidemiological studies, an association is reported between respiratory infections and the pathogenesis of bronchial asthma [22]. In addition, samples collected by bronchoscopy or induced sputum indicate a relation between asthma and microbial infection of the airway pathogens, including common bacteria such as *Proteobacteria*, *Bacteroidetes*, and *Firmicutes* [23]. Based on these previous observations, we hypothesize that TCM treatment modulates airway micro-organisms, and changes both airway microbiome composition and function, thereby impacting the symptoms of asthma. To the best of our knowledge, changes in microbiome composition in the airways of asthma patients with TCM treatment have not yet been fully characterized.

In previous studies, it is shown that JWYH therapy improves the symptoms of asthma and prevents the condition from worsening [18]. However, no data are available from large-scale randomized controlled trials (RCTs) on the efficacy of JWYH and its adverse effects. Therefore, we aim to perform the first double-blinded, randomized, placebo-controlled trial to determine the effectiveness and safety of JWYH treatment for persistent asthma.

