### Setting

This clinical trial will be conducted in eight clinical centers in Shanghai: Longhua Hospital affiliated Shanghai University of TCM, Fengxian District TCM Hospital, Jing’an Centralized Hospital, Pudong Hospital, Eighth People’s Hospital of Shanghai, Shanghai TCM-Integrated Hospital, Xuhui Centeralized Hospital, and the Fudan University affiliated Zhongshan Hospital. Prior to the trial, all personnel are trained in the Longhua Hospital to ensure that the multicenter physicians and staff involved in the trial fully understand all aspects of the trial.

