### Exploratory outcome

ACT score at week 16

Microbial diversity: We hypothesize that airway microbiota is different among TCM treatment and control groups regarding changes in microbial diversity. The composition and structure of the microbiome in induced sputum will be tracked using high-throughput *16SrRNA*-based gene analysis. Diversity index of evenness, richness, and abundance will be calculated to summarize and compare microbiomes at the operational taxonomic unit (OTU) level.

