Where appropriate, subgroup analyses, will be provided for effectiveness and safety endpoints, and will be based on baseline disease characteristics.

Data are analyzed using SAS 9.4 software (SAS Institute Inc., Cary, NC, USA). Unless otherwise noted, all treatment effects are employed at a two-sided α level of 0.05 and confidence intervals (CIs) will be calculated at 95%, two-sided.

For exploratory analysis of the airway microbiome, alpha diversity will be estimated as the number of observed OTUs and by the Chao1 Index, Simpson Index, Shannon Index, and phylogenetic alpha diversity (PD). UniFrac beta-diversity metrics will be compared between treatment groups using the PERMANOVA test from R’s vegan library [33]. In addition, UniFrac measures the phylogenetic distance between two samples as the fraction of the branch length of the phylogenetic tree, and are widely used to determine whether communities are significantly different [34]. Community dissimilarities will be estimated using principal coordinates analysis (PCoA). OTU abundance differences will be analyzed by assuming rarefied (Fisher’s exact test, respectively) and non-rarefied (metagenomeSeq zero-inflated Gaussian [35]) data. Statistical significance is determined by permutation tests using 10,000 permutations. In addition, core microbiome analyses will be performed to identify resident bacteria, after applying Benjamini-Hochberg FDR adjustments for multiple comparisons.

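### The UniFrac PERMANOVA names only treatment: with unequal usable samples a positive result need not be a shift in average composition, and leaving out hospital can cost power

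*Protocol article*

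**What the plan says.** The microbiome work is labelled exploratory: "For exploratory analysis of the airway microbiome, alpha diversity will be estimated as the number of observed OTUs" and by several indices. For community differences the Protocol article (Statistical methods) states that "UniFrac beta-diversity metrics will be compared between treatment groups using the PERMANOVA test", using R's vegan library, and describes UniFrac as "widely used to determine whether communities are significantly different". Principal coordinates analysis (PCoA) is also planned. On inference: "Statistical significance is determined by permutation tests using 10,000 permutations".

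Under Exploratory outcome, "The composition and structure of the microbiome in induced sputum will be tracked". The Background hypothesizes that treatment changes microbiome composition and function, and the Discussion says the trial will investigate changes in microbial composition.

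On hospitals, the Setting section says: "This clinical trial will be conducted in eight clinical centers in Shanghai". The clinical ANCOVA considers center; the microbiome comparison does not mention it.

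**The concern.** PERMANOVA is the only formal test of whole-community difference that the article names. Two features limit what it delivers as written.

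- **Meaning of a rejection.** The test can reject when arms share the same average community but differ in spread between patients. It does so most readily when the smaller group is the more variable one. Usable sample counts could become unequal: 20% dropout is expected, each visit needs a usable induced sputum, and the Background reports that "the JWYH formula significantly improves cough and sputum symptoms". A difference in spread could then be reported as a change in composition.
- **Precision.** Any hospital difference in the samples stays in the residual if center is not in the model, and a real shift becomes harder to detect.

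**Working it through.** **Inputs from the article:** three arms allocated 1:1:1; eight hospitals; sputum at randomization and weeks 2, 4 and 8; two-sided alpha 0.05; 64 evaluable patients per arm.

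**The plan's own figure (primary endpoint).** n per arm = 2(1.96 + 0.84)² × 4² / 2² ≈ 63, or 64 with the t distribution. 64 / 0.8 = 80 per arm, 240 in total. This reproduces. The article gives no size or power figure for the PERMANOVA, so everything below rests on assumed spread ratios, shifts and hospital shares, with Euclidean coordinates standing in for UniFrac.

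**1. Why arm sizes matter.** Per axis, with no shift, k arms, sizes n_g (sum N) and variances σ_g²:

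- expected among-arm sum of squares: B = Σ(1 − n_g/N)σ_g²
- its expectation when labels are permuted: P = (k − 1) Σ n_g σ_g² / N

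With one arm's SD at 2 (variance 4) and the others at 1:

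- 64/64/64: B = (2/3)(1 + 1 + 4) = 4.00; P = 2 × (6/3) = 4.00; B/P = 1.00
- 64/64/50, smallest arm variable: B = 2(1 − 64/178) + 4(1 − 50/178) = 4.16; P = 2(128 + 200)/178 = 3.69; B/P = 1.13
- 50/50/64, largest arm variable: B = 2(1 − 50/164) + 4(1 − 64/164) = 3.83; P = 2(100 + 256)/164 = 4.34; B/P = 0.88

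So equal arms leave the statistic centred, a small variable arm pushes it up, and a large variable arm pulls it down.

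**2. Simulated rejection without a shift** (5 or 20 axes, 199-299 permutations, mostly 2,000 data sets per setting):

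| Usable samples | Variable arm | SD ratio 1.5 | SD ratio 2 |
|---|---|---|---|
| 64/64/64 or 80/80/80 | any one | 5.0-6.7% | 6.4-7.2% |
| 48/64/64 | smallest | 7.5% | 11.8% |
| 64/64/50 | smallest | 8.7-10.6% | 11.4-16.1% |
| 50/50/64 | largest | 3.2% | 2.0% |

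Other runs with the smaller arm more variable reached about 18%. A harsher imbalance (70/64/45, 600 data sets) gave 15% and 25%. If both JWYH arms shrink (48/48/64), rejection is 10.6% when they are 1.5 times as variable, 2.5% when placebo is, and 5.1% with equal spread.

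**3. Leaving out hospital.** Let hospital explain a share c of the variation. If arms are balanced within hospital, B carries no hospital part while P does, so B/P is about 1 − c and the test is conservative. Simulated size was 0.1-3.4% for c of 5-30%. Without such balance it was 4.4-6.1%. It is not inflated in either case.

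Power, three arms of 64, shift of 0.8 SD on one of 20 axes, within-hospital variation held fixed (plain test, then center-adjusted with permutation within center):

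| Hospital share | 0 | 5% | 10% | 20% | 30% |
|---|---|---|---|---|---|
| Arms not balanced by hospital | 77 / 77 | 74 / 76 | 73 / 75 | 61 / 78 | 51 / 79 |
| Arms balanced by hospital | 79 / 79 | 71 / 80 | 65 / 80 | 40 / 79 | 19 / 79 |

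A second setup (two arms of 64, hospitals of unequal size) gave 74/71, 73/75, 75/80 and 74/85 at shares of 0, 10, 20 and 30%. Its plain-test power stays flat, as expected if total variation is held fixed. The direction agrees; the size depends on the setup.

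**4. One fix does not replace the other.** With center adjusted, 64/64/50 usable samples, the smallest arm 1.5 times as variable and a 10% hospital share, rejection without a shift was still 9.4%.

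**The case against.** The best objection is that the point rests on silence. The article does not say that treatment is the only term or that permutation is unrestricted, and such details of an exploratory analysis are often left to a full protocol or SAP. That stands as far as it goes: the absence is not proof of omission, and nothing in the section is contradictory. But the article does specify the test, the groups compared, the library and the permutation count, and it deals with center for the clinical outcomes. The specification as printed can be improved at almost no cost.

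The unequal-arm case is also uncertain. Allocation is 1:1:1, sputum is induced, and patients with a contraindication to induction are excluded. Nothing in the article indicates which arm would be more variable, and in the opposite direction the test is conservative. This stands, and it is why the point is conditional.

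A reader might infer that a significant PERMANOVA cannot be read as a composition change at all. The article does not support that: with near-equal arms the level for a shift stays at about 5-7%. Under randomization, a rejection driven by spread is still evidence of some treatment effect on the communities. A reader might also infer that omitting hospital biases the comparison or creates false positives; it does neither.

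Finally, it is tempting to allow a shift claim only when the dispersion test is non-significant. That would do harm. With 64/64/64 and one arm only 1.2 times as variable (20 axes), PERMANOVA rejected without a shift in 5.6% of trials and had 84% power for a real one, yet the dispersion test was significant in every trial. Nor does a non-significant dispersion test prove equal spread.

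**Conclusion.** The point holds in a limited form. As written, the test is valid under the null of no treatment effect of any kind and close to nominal for a shift when usable samples stay near 1:1:1. If samples become unequal and the smaller arm is 1.5 to 2 times as variable, it rejects in roughly 7-18% of trials with no shift in average composition, so the result alone does not separate location from spread.

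Omitting hospital costs only power. Without balance by hospital, the loss is about 2 points at a 10% hospital share and 5 to 17 points at 20%, depending on what is held fixed; it is larger if arms are balanced within hospital. Adjusting costs about 2-3 points at most if hospitals do not differ. Because the analysis is exploratory, this is an inexpensive improvement and does not threaten the trial's main conclusions.

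**What to change.** In Statistical methods, for each sputum visit with one sample per patient:

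- Enter center before treatment in the PERMANOVA and permute within center.
- Beside each PERMANOVA, report a permutation test of multivariate dispersion between arms (available in the same vegan library) and the number of usable samples per arm.
- Interpret both together with the PCoA. When dispersion differs and arm sizes are clearly unequal, describe a significant PERMANOVA as a difference in location and/or spread. When arms are balanced, do not withhold a shift claim merely because the dispersion test is significant.

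The cost is a few lines of code, a sentence or two of text and the small power loss noted above if hospitals do not differ. No new data are needed. The article describes a trial that is still recruiting, so the change can be fixed before analysis.

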### Collection of sputum

At the time of randomization, samples of induced sputum will be collected from subjects, as well as at 2 weeks, 4 weeks, and 8 weeks after enrollment. From each subject, sputum will be induced by inhalation of a nebulized solution of 3% saline. To minimize oral contamination, patients rinse their mouth and clean their nasal passages before sputum induction. Sputum samples are collected into sterile cups, and the entire procedure lasts about 15 min. Sputum plugs are selected and differential cell counting is performed. An equal weight of dithiothreitol is added to the sputum plug to dissolve mucus. All samples will be stored at − 80 °C prior to bacterial deoxyribonucleic acid (DNA) extraction.

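### Fisher's exact test on rarefied OTU data either counts sequencing reads as if they were patients or does not test abundance, and no stated microbiome test uses the baseline sputum sample

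*Protocol article*

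**What the plan says.** The Exploratory outcome section hypothesises that "airway microbiota is different among TCM treatment and control groups regarding changes in microbial diversity". Under Collection of sputum, "samples of induced sputum will be collected from subjects, as well as at 2 weeks, 4 weeks, and 8 weeks after enrollment", the first at randomization, so each patient can give four samples, one of them before treatment.

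The Statistical methods section then sets out the analysis:

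- Alpha diversity is to be estimated by several indices. No between-group test is tied to them.
- "UniFrac beta-diversity metrics will be compared between treatment groups using the PERMANOVA test", with no visit, baseline term or permutation unit named.
- "OTU abundance differences will be analyzed by assuming rarefied" data, for which Fisher's exact test is named, and non-rarefied data, for which a zero-inflated Gaussian model is named.
- "Statistical significance is determined by permutation tests using 10,000 permutations", again without saying what is permuted.
- The Benjamini-Hochberg adjustment is mentioned in the sentence on the core microbiome, not in the one on OTU abundance.

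The general rule is that "all treatment effects are employed at a two-sided α level of 0.05". The microbiome work is labelled exploratory, but the Abstract and the Study design section present the link between airway microbiome and treatment as one of the trial's aims.

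**The concern.** Fisher's exact test works on a two-by-two table of independent units. With rarefied OTU data, such a table can be filled in two ways.

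1. **Reads.** The cells hold reads of the OTU and all other reads, summed by arm. Tens of thousands of reads then stand in for 64 patients. Reads from one patient share that patient's airway flora, so the effective sample size is far smaller than the table implies and p-values are too small.
2. **Patients.** The cells hold patients with and without the OTU. The unit is right, but an OTU present in nearly everyone can differ several-fold in abundance without the test seeing it.

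Neither does what the sentence promises, which is a valid test of abundance. This is a choice of method that the article states, not a detail it leaves out.

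The second problem is a mismatch between question and test. The hypothesis concerns change and a pre-treatment sample is collected, but the stated tests compare groups without it. At stake is whether the taxa reported as differing between JWYH and placebo can be believed, and whether the question about change is answered at all.

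**Working it through.** **The plan's own figure.** The article gives no operating characteristics for the microbiome tests. Its sample size reproduces and supplies the patient numbers used here. For an ACT difference of 2 with SD 4, two-sided 5% and 80% power, the t-test needs 63.8, so 64 per group. Then 64 / 0.8 = 80 per group, and 3 × 80 = 240.

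**Inputs.**

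- From the article: 64 patients per arm, four samples per patient, nominal level 0.05 two-sided.
- Assumed, because the article gives none: 1,000 reads per patient after rarefying (5,000 as a variant); OTU mean abundance 1% or 5%; correlation ρ between reads of one patient, 0.001 to 0.05.

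**Step 1: closed form.** With m reads per patient, the variance of a pooled proportion is inflated by D = 1 + (m − 1)ρ. A test that ignores this rejects under the null with probability 2[1 − Φ(1.96/√D)]. For m = 1,000:

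| ρ | D | 1.96/√D | Null rejection |
|---|---|---|---|
| 0 | 1 | 1.96 | 5% |
| 0.001 | 1 + 999 × 0.001 = 2.00 | 1.39 | 17% |
| 0.01 | 1 + 999 × 0.01 = 10.99 | 0.59 | 55% |
| 0.05 | 1 + 999 × 0.05 = 50.95 | 0.27 | 78% |

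**Step 2: simulation.** Setup: beta-binomial variation between patients, no treatment effect, one sample per patient, 64 per arm, 1,000 reads. Reads were pooled by arm and tested with a continuity-corrected chi-square, which is close to Fisher's test at these counts. Two runs (1,000 and 2,000 replicates) gave:

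| OTU mean | ρ | Reads as units | Patient-level rank test |
|---|---|---|---|
| 1% | 0.001 | 16–17% | 5–6% |
| 1% | 0.01 | 54–55% | 5% |
| 5% | 0.01 | 54–56% | 4–7% |
| 5% | 0.05 | 76–80% | 4–5% |

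At ρ = 0 the read-level test returned 4.9%, so the excess comes from treating reads as independent. At 5,000 reads the error is larger: 40% at ρ = 0.001 and 91% at ρ = 0.05.

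**Step 3: what would rescue the Fisher statistic.** Permuting arm labels across patients (499 permutations, 2,000 replicates) gave 4.6% to 5.5% in the same four settings. Fisher's test on presence or absence per patient rejected in 0% to 3.3% of runs over all settings tried, which is valid and conservative.

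**Step 4: repeated samples, only if pooled.** PERMANOVA was simulated with three arms, 64 patients per arm and four samples each, using Euclidean distance in place of UniFrac. With all samples permuted freely, the null rejection rate was 4% at within-patient correlation 0, 34% at 0.2, 62% at 0.4 and 79% at 0.6. With whole patients permuted it was 4.0% to 5.8%.

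**Step 5: baseline.** Set side by side, the hypothesis is about change, the first sample is taken at randomization, and the stated tests compare groups with no change score or baseline covariate. For ACT, the same section specifies baseline adjustment and contrast days.

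**The case against.** **The permutation sentence may already solve the read problem.** It follows directly after the OTU tests. If patient labels are permuted, the Fisher statistic is correctly calibrated. This stands as a possibility, and Step 3 confirms it. But the text does not say what is permuted, and an exact test supplies its own p-value. The percentages therefore hold only if that p-value is taken from read counts.

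**The wording is loose, and Fisher's test may be meant for presence or absence.** That version is valid, but then the sentence does not describe a test of abundance.

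**A reader might infer that four samples per patient will be pooled and freely permuted in PERMANOVA.** The article does not say so. A PERMANOVA at a single visit has one sample per patient and is valid, and an article may leave such detail to the full protocol. Step 4 is a warning about one possible implementation, not a finding about the plan.

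**A reader might also infer that chance baseline imbalance would produce excess false positives.** It would not. Under randomization, an unadjusted patient-level comparison keeps its 5% level. What is lost by ignoring baseline is precision and the match to the hypothesis.

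**Nor does it follow that most reported differences would be false.** A null rejection rate is not the share of reported findings that are wrong; that share also depends on how many OTUs truly change.

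**The outcome is exploratory.** True, and this limits the reach. Exploratory status excuses low power and looser multiplicity control, but not a test whose unit is wrong. The zero-inflated Gaussian analysis of non-rarefied data, named in the same sentence, was not examined here.

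**Conclusion.** The point holds in limited form. Fisher's exact test is unsuited to OTU abundance on rarefied data. On reads, the null rejection rate would be about 16% to 76% or slightly more instead of 5%, assuming 1,000 reads per patient, read correlation 0.001 to 0.05, 64 patients per arm and p-values not calibrated by permuting patients. Greater depth or correlation makes it worse; only if patients do not differ at all does it return to 5%. On presence or absence the test is sound but answers another question.

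The failure to use baseline in the stated between-group tests is a separate, milder fault: lower precision, and a hypothesis about change left untested. The primary ACT analysis and its ordered testing of the two doses are untouched.

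**What to change.** Revise the microbiome paragraph as follows:

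- **OTU abundance:** replace Fisher's test with a patient-level test, for example a rank test on each patient's change from baseline, or a negative binomial model with one value per patient per visit. If presence or absence is also of interest, keep Fisher's test for that and label it so.
- **Alpha diversity:** compare arms at week 4, then week 8, by ANCOVA with the patient's baseline index as covariate.
- **UniFrac:** run PERMANOVA separately at each named visit. If visits are pooled, permute whole patients.
- **Multiplicity:** apply Benjamini-Hochberg to all OTUs tested, and say so in the sentence on OTU abundance.

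The cost is one paragraph, some extra analysis code and probably fewer significant OTUs. The samples needed are already in the collection schedule.
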